### Interventions

Our study has a two-component intervention package, including a 30-min daily BLT (green and red lights for the treatment and control groups, respectively) and a sleep hygiene educational package for 4 weeks. The bright light visor (Feel Bright Light Model 100, Physician Engineered Products, Fryeburg, ME) will be used for the treatment group; however, the visor delivers blue–green light, thus we blocked the blue light and remind the participants to use the green light to prevent potential damage to eyes, especially the elderly. The unit weighs approximately 1.7 ounces, is comfortable to wear, and is powered by a rechargeable battery, allowing participants to move freely for their daily work. Participants will undergo 30 min of BLT within an hour of waking up for 4 weeks. A red-light visor (Physician Engineered Products, Fryeburg, ME), an attention control strategy, that does not have any therapeutic effect will be used for the control group. Both groups will receive a sleep hygiene educational booklet.

Sleep hygiene is fundamental to improving sleep and is considered an important intervention to promote sleep (McCurry et al., 2004). Sleep B.E.T.T.E.R. will be included in this educational package. This booklet includes information on normal sleep and promoting the homeostatic drive for sleep using the following six basic guidelines: bedroom environment, regular daily exercise, reducing tension and stress, time trying to sleep, eating and drinking, and maintaining regular day–night rhythms.

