## Materials and methods

### Study design

This parallel, randomized, double-blind, placebo-controlled clinical trial will be conducted at a teaching hospital in the middle part of Taiwan. The sample will consist of 60 women diagnosed with migraine and sleep disorders. After a 1:1 random assignment, 30 women will be assigned to light therapy and sleep hygiene education, and the other 30 women will be assigned to placebo light and sleep hygiene education for a 4-week clinical trial (Figure 1).

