### Inclusion and exclusion criteria

The inclusion criteria are as follows: diagnosed with migraine according to the International Classification of Headache Disorder 3rd edition (ICHD-3); aged 20–65 years; with sleep disorders (PSQI >5 points); willing to participate in activity monitoring (wrist recorder) during the day and night for 9 consecutive weeks, and one night in the sleep room for polysomnography, totaling to two time periods (before and after treatment); willingness to have blood drawn twice; not allergic to metals (a contraindication to wearing wrist actigraph); and not currently participating in other interventional trials.

The exclusion criteria are as follows: non-migraine headaches (e.g., tension-type or secondary headaches, among others); major head trauma in the past; alcoholism within 1 year; (4) pregnant or breastfeeding women; (5) cannot cooperate with the test progress; (6) allergic to light; and (7) taking beta-blockers, antiepileptic drugs, calcium ion blockers, antidepressants, onabotulinumtoxinA, CGRP monoclonal antibody, and hormone preparations in the past month.

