### Ethical considerations

The study was approved by the Institutional Review Board of Kuang Tien General Hospital (KTGH21002) and registered in the ClinicalTrials.gov (NCT4890691).

Participation in research is voluntary. Completing the data booklets may result in some discomfort as women will reflect on the answers that they will provide; they will be reminded that they may stop at any time. Women wearing the bright light visor may have a slight chance of developing a headache similar to exposure to natural sunlight; if so, participants will be instructed to use the 8,000 lux instead of 12,000 lux. During the weekly follow-up phone call, participants will be asked if they have any unusual symptoms. If yes, this will be discussed with the Co-PI, who is a neurologist, and, if any adverse symptoms are noted, the participant will be requested to discontinue the light treatment. All participants may choose to terminate their participation at any time without incurring any adverse consequences.

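### The protocol names possible eye damage from the visor light, but none of its 14 listed entry criteria asks about known eye disease

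*Protocol article*

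**What the plan says.** Under Interventions, the article explains that "the visor delivers blue–green light" and gives the response: "thus we blocked the blue light and remind the participants to use the green light to prevent potential damage to eyes, especially the elderly". The dosing rule is "Participants will undergo 30 min of BLT within an hour of waking up for 4 weeks". The intensity appears only under Ethical considerations, where women who develop a headache step down: "participants will be instructed to use the 8,000 lux instead of 12,000 lux". The article does not say whether these figures apply before or after the blue light is blocked.

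The criteria section gives itemised lists. One item screens for a risk specific to a device, the actigraph: "not allergic to metals (a contraindication to wearing wrist actigraph". The items closest to the visor are "5) cannot cooperate with the test progress; (6) allergic to light".

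During treatment, a weekly call asks about unusual symptoms, which are discussed with a neurologist, and "if any adverse symptoms are noted, the participant will be requested to discontinue the light treatment".

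**The concern.** The protocol itself names the eye as an organ at possible risk from the light source, yet its entry criteria contain no question about the eye. It does screen for a contraindication to the measuring device worn on the wrist, but has no eye-history item for the device that delivers light to the eyes.

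What is at stake is who is exposed. The weekly call and the stopping rule act only once exposure has begun, whereas eye disease that is already known can be identified before assignment. The trial's estimates, sample size and analysis are not affected.

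**Working it through.** The plan gives no figure to reproduce here. The check is a count of the criteria, a comparison of the safeguards, and a sensitivity calculation on assumed prevalences.

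**Count of criteria (Inclusion and exclusion criteria).**
- Inclusion: ICHD-3 migraine; age 20–65; PSQI above 5; willing to have actigraphy and polysomnography; willing to give blood twice; no metal allergy; not in another interventional trial. That is 7.
- Exclusion: non-migraine headache; past major head trauma; alcoholism within a year; pregnancy or breastfeeding; unable to cooperate; light allergy; listed drugs in the past month. That is 7.
- Total 7 + 7 = 14. Items on a contraindication to the wrist device: 1. Items on light: 1 (light allergy). Items on eye disease: 0. Items leaving a safety exclusion to the investigator's judgement: 0.

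**Do other parts of the article fill the gap?**
- Blocking blue acts before exposure and on the hazard that the article ties to the visor's light. The reminder acts during exposure and depends on the participant.
- The light-allergy exclusion acts at entry, but a woman with known retinal disease need not be allergic to light.
- The step-down to 8,000 lux is triggered by headache, not by eye symptoms.
- The weekly call and the stopping rule come after the start and are not specific to the eye.
- Table 1 lists no eye assessment. It does list eligibility screening and medical records at pretest, so there is already a place to ask.

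**Size, under assumption.** The article gives neither a prevalence of eye disease nor an ocular threshold. Let *p* be the assumed share of otherwise eligible women with known eye disease of concern. Inputs from Study design: "The sample will consist of 60 women diagnosed with migraine and sleep disorders", with 30 assigned to the treatment light.

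- Expected number in the green arm = 30*p*
- Chance of at least one in that arm = 1 − (1 − *p*)^30
- Extra women needed to reach 60 if they are excluded = 60/(1 − *p*) − 60

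| Assumed *p* | Expected in green arm | Chance of at least one | Extra women needed |
|---|---|---|---|
| 0.5% | 0.15 | 1 − 0.995^30 = 14% | 60/0.995 − 60 = 0.3 |
| 1% | 0.30 | 1 − 0.99^30 = 26% | 60/0.99 − 60 = 0.6 |
| 2% | 0.60 | 1 − 0.98^30 = 45% | 60/0.98 − 60 = 1.2 |
| 5% | 1.50 | 1 − 0.95^30 = 79% | 60/0.95 − 60 = 3.2 |

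Rounded up, the last column is 1 to 4 women. The third column is the chance of enrolling and exposing such a woman; it says nothing about injury.

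**The case against.** The strongest reply is that this is an omission from a condensed article, not an error. The printed list may be incomplete: the restriction to women appears under Study design and not among the criteria. That is fair, and the full protocol may contain an eye item. But the article did not leave eligibility to another document. It printed an itemised list down to metal allergy and seven kinds of medication, and under that list a woman with known retinal disease qualifies.

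The second reply is that the named hazard is already dealt with. Blue is blocked, the article does not say that green light harms the eye, and it states no eye contraindication for the visor as it does metal allergy for the actigraph. All of this is correct, and it keeps the point small. The case for a screening question does not rest on green light being harmful. It rests on the article naming an eye risk and relying in part on a reminder to control it.

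The third reply is that the prevalences have no anchor in the document and the resulting range is wide. That also stands. The range shows only that enrolling such a woman is not remote under modest assumptions, and that excluding her costs little.

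**Conclusion.** The point holds as a minor, precautionary gap, worth considering. It is certain that 0 of the 14 listed criteria concern eye disease and that the in-trial safeguards act only after exposure starts. It is not known whether the full protocol already screens for this, or whether the light with blue blocked poses any risk to women with eye disease.

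Under assumed prevalences of 0.5% to 5%, between 0.15 and 1.5 such women would be expected in the green arm. No harm is quantified. Short daily sessions over 4 weeks, the age cap of 65 and the weekly calls all limit the concern.

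**What to change.** Add one exclusion to the criteria: known retinal disease, or other eye disease or eye surgery that the investigators judge makes bright light unsafe. Ask it as a history question at the existing eligibility screening and check it against the medical records already collected at pretest. Apply it to all women before assignment, so that both arms are drawn from the same population. Because the second half of the exclusion rests on judgement, the investigators should name the conditions they have in mind. If the full protocol already asks about eye disease, it is enough to state it in the list.

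The cost is one eligibility line and one question, with no eye examination and no extra visit. Under the assumed 0.5% to 5%, about 1 to 4 more women would have to be found to reach 60.

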### Participant recruitment

A research assistant (RA) under a neurologist’s supervision will screen the visiting log at the research site’s migraine clinic to identify potential participants. Then, the RA will approach the women and describe the study. The opportunity will be given to the women to privately consider the project, and a later contact will be made to answer questions and enroll the women interested in participating.

### Data collection

Apart from the demographic form, psychometric sound instruments will be used in the study, which are described below (Table 1).

**Table 1 tab1:** Measurement schedule.

	Baseline	Treatment and data collection timepoints			
Timepoint	Pretest	1st week	2nd week	3rd week	4th week
Enrolment					
Eligibility screening	X				
Informed consent	X				
Demographics	X				
Medical records	X				
MEASUREMENTS					
4-week headache diary	X X X X	X	X	X	X
PGI-I	X				X
PGI-S	X				X
MIDAS	X				X
HADS	X				X
ESS	X				X
PSQI	X				X
GSDS	X				X
7-day wrist actigraphy	X				X
7-day sleep diary	X				X
Overnight PSG	X				X
Blood sample	X				X
Weekly phone call		X	X	X	X

PGI-I, Patient Global Impression of Improvement; PGI-S, Patient Global Impression of Severity; MIDAS, Migraine Disability Assessment; HADS, Hospital Anxiety and Depression Scale; ESS, Epworth Sleepiness Scale; PSQI, Pittsburgh Sleep Quality Questionnaire; GSDS, General Sleep Disturbance Scale; PSG, Polysomnography.

#### Headache diaries

This diary includes headache days, duration, intensity, frequency, location, characteristics, use of pain medication, accompanying symptoms and triggers, among others. Each diary covers 28 days.

#### Detection of headache-related scales

Patient Global Impression of Improvement (PGI-I) is an assessment to measure disease improvement (Guy, 1993). PGI of Severity (PGI-S) will be used to measure the severity of migraine (Guy, 1993). The Migraine Disability Assessment (MIDAS) (Stewart et al., 1999) will be used to assess migraine-related disabilities in different areas of life in the past 3 months.

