**Methods and analysis:**

This project is a 2-year, randomized, double-blind, placebo-controlled clinical trial. The study design includes a 4-week monitoring period (baseline and pretest), a 4-week treatment period, and a posttest. The study participants will undergo assessments on headache frequency and severity and subjective and objective (wrist actigraphy and polysomnography) sleep disturbances, and quality of life and a series of blood tests for serum biomarkers.

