### Objectives

The specific goals of this prospective study are to (1) compare the effects of BLT (green light and sleep hygiene) with an attention control treatment (placebo light and sleep hygiene) on selected sleep variables [total nocturnal sleep time, wake after sleep onset (WASO), sleep efficiency, daytime sleepiness], migraine conditions (frequency and severity), and QOL (mental health) from baseline to 1 month after beginning the intervention; and (2) explore the light therapy’s molecular and biochemical effects on migraine prevention.

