### Data management

The following information will be obtained from each subject: demographics, 4-week headache data (pre and posttreatment), pre and posttreatment outcome variables (PGI-I, PGI-S, MIDAS, HADS, PSQI, and GSDS), selected physiological indicators (PSG, CGRP, and PACAP), and pre and posttreatment 7-day wrist actigraphy data (TST, WASO, circadian activity rhythm). The physiological analysis will be performed in the hospital’s laboratory using established laboratory protocols for specimen processing and analysis. Assay preparation will be performed following the manufacturer’s instructions. The sleep data obtained with the watch will be analyzed by using the Action 4 software, and the PSG will be analyzed by using the Crystal software.

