### Data analysis

All data analyzes will be conducted using the intent-to-treat principle. When considering the results of multiple comparisons, the Bonferroni correction will be used to correct the significance level. Pre and posttest, the related scales of the experimental and control groups, such as the headache diary, PGI-I, PGI-S, MIDAS, HADS, PSQI, ESS, GSDS, and PSG, wrist actigraphy, and blood test analysis, will be expressed as mean ± standard deviation.

The above-mentioned scales and blood test values of the pre and posttreatment assessments of each patient will be tested with the Sign test to identify any difference before and after the test. Finally, the generalized estimating equation model will be used to evaluate whether the experimental group significantly had reduced pain frequency and severity and improved sleep than the control group to understand the effect of light therapy on migraine.

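### MIDAS recalls 3 months but is repeated at treatment week 4, so only about 31% of the posttest window is on treatment and the score understates any effect on disability

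*Protocol article*

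**What the plan says.** All references are to the protocol article.

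- **Recall.** Under Detection of headache-related scales, MIDAS "will be used to assess migraine-related disabilities in different areas of life in the past 3 months".
- **Timing.** Table 1 (Data collection) marks MIDAS at pretest and in the 4th treatment week, and nowhere else. The abstract's Methods and analysis describes "a 4-week treatment period, and a posttest", and Interventions says "Participants will undergo 30 min of BLT within an hour of waking up for 4 weeks". The Objectives compare the arms "from baseline to 1 month after beginning the intervention".
- **Use.** Data management places MIDAS among the "pre and posttreatment outcome variables (PGI-I, PGI-S, MIDAS, HADS, PSQI, and GSDS". Under Data analysis, the scales "will be tested with the Sign test to identify any difference before and after the test". A generalized estimating equation (GEE) model then compares the arms on pain frequency and severity and on sleep.

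No later MIDAS and no short-recall version is mentioned. The other recall periods that the article states fit a 4-week trial: 28 days for the headache diary, one month for the PSQI, one week for the GSDS.

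**The concern.** A questionnaire that looks back three months, given at the end of four weeks of treatment, mostly asks about time before treatment. Some of that time has already been counted in the pretest score. MIDAS is the only scale that the article describes as measuring migraine-related disability, so no other listed scale would correct the picture. The risk is one of interpretation. A flat MIDAS could be reported as no effect on disability when the window alone could hide one. A fall in MIDAS would be reported at a fraction of its true size.

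**Working it through.** The article gives no effect size, SD, alpha or power for MIDAS, so there is no planned figure to reproduce. The window arithmetic needs only the stated periods. The power figures need assumptions, which are marked.

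**1. Share of the posttest window on treatment.** Take 3 months as 13 weeks = 91 days, with treatment from day 0 to day 28.
- On treatment: 28/91 = 30.8%. Before treatment: 63/91 = 69.2%.
- With 84 or 92 days of recall, the share before treatment is 66.7% or 69.6%.
- If the form is completed at day 22, early in the 4th week: 22/91 = 24.2% on treatment.
- The inclusion criteria ask for wrist monitoring "during the day and night for 9 consecutive weeks", which may mean 4 + 4 + 1 weeks. If the posttest falls at day 35, (91 − 35)/91 = 61.5% of the window still precedes treatment.

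**2. Overlap with the pretest.** The posttest covers days −63 to 28.
- Pretest at day 0 covers −91 to 0: 63 days are shared.
- Pretest at day −28 covers −119 to −28: 35 days are shared.

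**3. Dilution of the score.** Observed relative fall = true fall × 28/91.
- A true 50% fall shows as 0.50 × 0.308 = 15.4%.
- A true 30% fall shows as 0.30 × 0.308 = 9.2%.

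**4. What a pre/post difference recovers.** With accurate recall, shared days cancel.
- Pretest at day 0: post minus pre is the 28 treated days minus the 28 days from −91 to −63. This is a clean 28-against-28-day contrast.
- Pretest at day −28: the part unique to the posttest is 56 days, of which 28/56 = 50% are treated.

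**5. Illustrative worst case: posttest scores only.** Assumed: 30 per arm (Study design: "The sample will consist of 60 women diagnosed with migraine and sleep disorders", allocated 1:1), two-sided 5%, normal approximation, SD unchanged by the dilution.
- Detectable difference at 80% power = (1.96 + 0.84) × √(2/30) = 0.72 SD of the observed score, which is 0.72/0.308 ≈ 2.35 SD before dilution.
- Assumed true effect of 0.8 SD: power 87% undiluted, 16% diluted. For 0.5 SD: 49% and 9%.

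**6. Simulation that uses the pretest.** Assumed: 30 per arm; Poisson disability days averaging one per week, with gamma variation between patients (shape 2); 13-week windows; independent multiplicative recall error at each visit; 1,000 replications (simulation error at most √(0.25/1000) = 1.6 percentage points). Power of the baseline-adjusted comparison for a true halving:

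| Recall error | Pretest just before treatment | Pretest at start of baseline |
|---|---|---|
| none | 81.2% | 52.1% |
| 20% | 35.6% | 29.6% |
| 40% | 15.4% | 14.5% |

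Comparing posttest scores only gives 9 to 13% throughout. A baseline-adjusted 28-day count of the same disability days gives 93 to 95%. That count was simulated without recall error, so it is an upper bound for any 28-day questionnaire. The fair comparison for it is the first row of the table.

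**The case against.** The strongest reply is that dilution to 31% describes the posttest score alone, while the plan also uses the pretest. The Sign test works on each patient's pre and post values, and GEE would normally use both assessments. Under step 4 the overlap then helps: with accurate recall and a pretest just before treatment, the shared 63 days drop out. This stands. It rules out the inference, which a reader might draw from step 5, that the trial can barely detect an effect on disability. Those figures rest on a posttest-only comparison and on effect sizes that the article does not give. The article states neither recall error nor the pre/post correlation, and the answer depends on both.

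The reply does not remove the mismatch. Cancellation requires patients to recall the same nine weeks identically on two occasions, and step 6 shows the gain shrinking quickly with modest error. Even with perfect cancellation, the difference reflects 28 days of benefit on a score that is read as three months. The Sign test makes no comparison between arms, and the GEE sentence names pain and sleep, not disability.

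It is also fair to say that MIDAS is not called primary and that disability is absent from the Objectives, which list sleep variables, migraine frequency and severity, and quality of life (mental health). The headache diary covers 28 days and matches the treatment period. A reader might infer that the mismatch undermines the trial's main conclusions; the article does not support that.

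Nor would a null MIDAS result necessarily be an artefact, since the treatment may truly have no effect. The most that follows is that the two explanations could not be told apart.

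**Conclusion.** The mismatch between recall period and assessment time is in the text and does not depend on an unseen document. About 31% of the posttest window is on treatment (24% to 33% over the recall lengths and completion days tried within week 4), and 35 to 63 of 91 days are shared with the pretest. The score is diluted accordingly: a true halving appears as about a 15% fall. This assumes that disability is spread evenly over the window and that the effect begins with treatment.

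The size of the power loss is not established. For a true halving, the baseline-adjusted simulation runs from 81% down to about 15%, depending on recall error and the timing of the pretest. The posttest-only figures are a worst case under assumed effects. The point limits what can be concluded about disability, a supporting measure, and leaves the main objectives testable.

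**What to change.** Ask the disability items with a past-4-weeks recall at the end of the 28-day baseline and again at the end of treatment week 4. Each window then matches its headache diary, and the treated share of the posttest rises from 31% to 100%. Keep the standard three-month MIDAS at pretest only, as a baseline descriptor. Change the MIDAS row in Table 1 and the outcome list in Data management to match.

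The cost is a reworded form and a short edit to the schedule. The 4-week scores would not be comparable with published MIDAS scores or grades, and the article does not establish the measurement properties of the reworded form, so the report should say so.

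Postponing the standard form to three months after the start of treatment would remove the pretreatment days. With treatment ending at week 4, however, still only 28 of 91 days would be on treatment.

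If the standard form is kept at week 4, the plan should state that it will not be interpreted as the effect of 4 weeks of treatment, and should fix the day on which the pretest form is completed.
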